#### Recruitment {15}

Patients scheduled for TKA from the Department of Orthopedics, Second Affiliated Hospital, Guangzhou University of Chinese Medicine will be screened by the research team for participation based on the inclusion and exclusion criteria listed above. Those who satisfy the inclusion criteria and are willing to participate in this experiment will be provided details about study treatment, follow-up, and contact details for further information. Each participant will be informed of the benefits and possible risks, and they will be requested to sign the informed consent and an ethics committee-approved personal information sheet before their inclusion in the study. Recruitment began in October 2020.

### Assignment of interventions: allocation

#### Sequence generation {16a}

Random assignment will be performed by an independent investigator (DL) using a computer-generated blocked random-allocation sequence with a 1:1:1 ratio.

#### Concealment mechanism {16b}

Computer-generated numbers will be located in a sealed envelope containing the treatment information.

#### Implementation {16c}

An independent investigator (DL) will allocate the participants to the groups using the sequences generated by the computer. He will not participate in the enrollment and assessment processes. Following anesthesia, an envelope will be opened by DL and an assisting nurse who is not involved in the study, and either of them will prepare the cocktail analgesics in another room based on the assigned envelope.

### Assignment of interventions: Blinding

#### Who will be blinded {17a}

Patients will be blinded owing to general anesthesia induction. Milky white flurbiprofen axetil injection will be used as an ingredient of cocktail analgesics, which will guarantee that there are no differences in the appearance of the three groups; thus, the surgeon will be blinded. The investigators (CZ, LZ, and XL) responsible for data collection and data analysis will be blinded to the random allocation.

#### Procedure for unblinding if needed {17b}

Unblinding is permissible only when a SAE or emergency rescue occurs.

### Data collection and management

#### Plans for assessment and collection of outcomes {18a}

Before the trial, all the researchers will be trained for proficiency in the test procedures and operations. The questionnaires and laboratory tests, which will be used in this study, have been widely used in previous studies, and their reliability and validity have been reported previously.

#### Plans to promote participant retention and complete follow-up {18b}

As a routine follow-up plan, participants will be advised follow-up clinic visits at 2 weeks, 4 weeks, 8 weeks, and 3 months; investigators will contact participants for clinical follow-up.

#### Data management {19}

EpiData 3.1, software will be used for data entry. To promote the quality and accuracy of data, double data entry and checking will be managed by two data administrators (CZ and LZ). The data obtained in this study will be stored in an electronic database. The data administrators and statisticians (XL) will be the only ones with access to the information. They will also be responsible for data backup. Original case report forms and any other records will be archived at The Second Affiliated Hospital, Guangzhou University of Chinese Medicine, for a minimum of 5 years from the completion of the study.

#### Confidentiality {27}

The information collected will be used for research purposes and analyzed without the identification of the individuals involved. All personal information of the potential and enrolled participants will not be shared or released. At the end of the trial, all information will be archived at the Second Affiliated Hospital, Guangzhou University of Chinese Medicine.

#### Plans for collection, laboratory evaluation, and storage of biological specimens for genetic or molecular analysis in this trial/future use {33}

CRP, IL-6, ESR, and Glu will be measured at the corresponding time points. All specimens will be destroyed after the examinations.

### Statistical methods

#### Statistical methods for primary and secondary outcomes {20a}

Perioperative outcomes will be summarized using the mean ± SD for continuous variables and the ratio for categorical variables. All statistical analyses will be conducted using the SPSS software (version 13.0. for Windows; SPSS, Inc., Chicago, USA). For continuous variables, the Kolmogorov–Smirnov test will be used to detect the normality of distribution. Analysis of variance (ANOVA) will be used to compare the differences among the three groups, and Dunnett’s *t* test will be conducted to compare the between-group differences. For categorical variables, the chi-square test will be conducted to compare the intragroup differences, and partitions of chi-square methods will be used to compare the between-group differences.

For repeatedly measured outcomes, multivariate analysis for repeated measures ANOVA test will be performed to compare the difference between the three groups, which contains the three intervention groups, time, and group-time interaction. Dunnett’s test will be applied for post hoc comparisons. When the group-time interaction showed a significant difference, a one-way repeated measures ANOVA was conducted to identify the difference in effect between the three intervention groups. The significance level will be set at *α*=0.05. Statistical analyses will be performed by an independent investigator.

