### Outcomes {12}

#### Primary outcome measures

The primary outcome will be knee pain during 90° flexion via VAS pain score measured by a 10-cm horizontal line scale [19]. The patients will be asked, “How much pain do you have this moment?”, the patient will then mark on the 10-cm horizontal line VAS. Zero means “absence of pain,” while 10 represents “the worst pain” VAS has been proven to be a valid and reliable outcome measure for recording pain with ICC = 0.96 to 0.98, according to a previous study [20]. The VAS score will be evaluated at preoperative day 1; postoperative 6, 24, 48, and 72 h; day 5; day 14; and day 30 following the surgery.

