### Secondary outcome measures

#### Postoperative 1-min walking ability

Physical activity is an important aspect of day-to-day life, and walking capacity is a measure of exercise tolerance that requires muscle strength. Walk tests measure the distance walked over a definite time period, with greater distances indicating better performance [21, 22]. The 1-min walk test will be measured on preoperative day 1, and POD 2, 5, 14, and 30. Participants will be asked to walk as fast as possible around a circular 20-m track over a period of 1 min. Rest breaks will be allowed if required. Walking aids can be used as required. The investigators will continuously assured that the track is consequently followed.

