#### Sample size {14}

The calculation of the sample size was based on previous studies. Ikeuchi et al. [13] reported that the POD 3 VAS scores were 27 ± 16 mm in the steroid group and 43 ± 18 mm in the control group. Kwon et al. [4] reported that POD 3 VAS scores were 35 mm in the steroid group and 41 mm in the control group. We assumed that the mean difference in the VAS score between the high-dose betamethasone group and control group was 0.8, and the mean difference between the normal-dose betamethasone group and control group was 0.4. An estimated standard deviation (SD) of 1.5, significance level (*α*) of 0.05, and power of test (*β*) of 0.8000 will be adopted. Based on the former data, the sample size was calculated as 69 participants per group. Assuming a dropout rate of 10%, the final sample size will be 78 participants per group, and 234 participants will be required for the three groups.

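### The stated repeated-measures model leaves out preoperative values that the trial collects; the analysis stays valid but may give away precision

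*Protocol article*

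**What the plan says.** Under Statistical methods {20a}, repeatedly measured outcomes are compared by a repeated-measures ANOVA "which contains the three intervention groups, time, and group-time interaction", with Dunnett's test for post hoc comparisons. Other continuous variables get a plain three-group ANOVA, again with Dunnett's test. The article mentions no baseline covariate, ANCOVA or change from baseline.

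The preoperative values are nevertheless collected:

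- **VAS** (Primary outcome measures): "The VAS score will be evaluated at preoperative day 1", followed in the same sentence by seven postoperative times.
- **Walking** (Postoperative 1-min walking ability): "The 1-min walk test will be measured on preoperative day 1, and POD 2, 5, 14, and 30".
- **Knee Society Score** (Other outcomes): preoperative day 1 and postoperative days 14 and 30.
- **Circumference** (Other outcomes): the sentence labels every listed day as preoperative. Read beside the Abstract, which gives days 2, 5, 14 and 30 after surgery, it sensibly means preoperative day 1 plus those four days.

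The protocol does not say whether the preoperative value is a level of the time factor. The Methods part of the Abstract lists the pain, walking, circumference and knee-score measurements to be recorded and analysed at postoperative times only.

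**The concern.** A preoperative measurement of the same quantity is usually the most obvious prognostic covariate available. Leaving it out puts the variance that it could explain into the error term and leaves chance baseline imbalance uncorrected. The sample size has no margin at its own assumptions: 69 per group gives almost exactly 80% power with an unadjusted SD. Any precision recovered from data already in hand is therefore worth having.

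A second, conditional issue concerns the definition of time. The cocktail is injected during surgery, so no treatment effect can exist at the preoperative visit. If that visit were one of the levels of time, the group main effect, and any Dunnett comparison built on it, would average in a visit with a true difference of zero.

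**Working it through.** **Inputs from Sample size {14}.** "We assumed that the mean difference in the VAS score between the high-dose betamethasone group and control group was 0.8"; "the mean difference between the normal-dose betamethasone group and control group was 0.4"; "An estimated standard deviation (SD) of 1.5"; "significance level (*α*) of 0.05"; "power of test (*β*) of 0.8000 will be adopted" (the power, although labelled β). Evaluable n is 69 per group. The correlation r between baseline and follow-up is **not in the document**; I assume 0.1 to 0.5.

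**Step 1: reproduce the plan's figure.** Take group means 0, 0.4 and 0.8 (grand mean 0.4). The sum of squared deviations is 0.16 + 0 + 0.16 = 0.32. The non-centrality of the three-group F test is

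λ = n × 0.32 / SD² = 69 × 0.32 / 2.25 = 9.81, with 2 and 3 × 69 − 3 = 204 degrees of freedom.

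Power is 0.8015. At 68 per group it is 0.795, so 69 is the smallest n that reaches 80%. The stated figure is reproduced exactly as an unadjusted three-group ANOVA.

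**Step 2: adjust for baseline.** The residual SD becomes 1.5 × √(1 − r²), so λ becomes 9.81 / (1 − r²). Error degrees of freedom fall from 204 to 203.

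| r (assumed) | Variance removed (r²) | Residual SD | λ | Power at 69 per group | n per group for 80% |
|---|---|---|---|---|---|
| none | 0 | 1.500 | 9.81 | 0.802 | 69 |
| 0.1 | 1% | 1.492 | 9.91 | 0.806 | 69 |
| 0.2 | 4% | 1.470 | 10.22 | 0.818 | 67 |
| 0.3 | 9% | 1.431 | 10.78 | 0.840 | 63 |
| 0.4 | 16% | 1.375 | 11.68 | 0.869 | 58 |
| 0.5 | 25% | 1.299 | 13.08 | 0.906 | 52 |

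**Step 3: sensitivity to the SD.** The first study cited in the sample size section had SDs of 16 and 18 mm. Pooled with equal weight this is √((16² + 18²)/2) = √290 = 17.0 mm, or 1.7 cm. With SD 1.7, unadjusted power is 0.689. Adjustment gives 0.694 at r = 0.1, 0.708 at r = 0.2 and 0.817 at r = 0.5.

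**Step 4: the conditional dilution.** Suppose the preoperative visit *were* a level of time and the treatment effect were constant over all postoperative visits. The group main effect would then be multiplied by (postoperative visits) / (all visits):

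- VAS: 7/8, so 0.8 becomes 0.70 and 0.4 becomes 0.35
- Walk and circumference: 4/5
- Knee Society Score: 2/3

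To size this for VAS, assume also compound symmetry with within-patient correlation ρ = 0.5 and SD 1.5.

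- **Baseline as a time level.** Variance of the eight-visit mean = 2.25 × (1 + 7 × 0.5)/8 = 1.266. The squared deviations of 0, 0.35 and 0.70 sum to 0.245, so λ = 69 × 0.245/1.266 = 13.36. Power 0.91.
- **Postoperative visits only, no covariate.** Variance = 2.25 × (1 + 6 × 0.5)/7 = 1.286, so λ = 69 × 0.32/1.286 = 17.17. Power 0.97.
- **Postoperative visits with baseline as covariate.** Variance = 1.286 − 2.25 × 0.5² = 0.723, so λ = 69 × 0.32/0.723 = 30.53. Power 0.999.

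**The case against.** The strongest reply is that nothing is stated incorrectly. The trial is randomised, the unadjusted comparison is valid, and the sample size was computed for exactly that analysis. Covariate lists are often left to the analysis plan, which is not shown. The validity argument stands in full. The argument from a missing analysis plan stands only in part: the protocol does not leave the model open but lists its terms, and baseline is not among them.

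A reader might infer that the group effect *is* diluted, because the VAS schedule puts the preoperative day in the same list as the postoperative times. The documents do not support that. That list is a measurement schedule; no section makes the preoperative value a level of time, and the Abstract's list of times is postoperative only. Moreover, the two harms exclude each other. If baseline were a time level it would be used, because the group-time interaction would then test whether change from baseline differs between groups; only the group main effect and comparisons resting on it would be diluted. If it is not a time level, there is no dilution.

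The size of the precision gain is also open to challenge. Whether preoperative arthritis pain predicts acute pain after surgery is not addressed in the protocol, and at r = 0.1 adjustment buys almost nothing. One might expect larger gains for walking, circumference and knee score, but the protocol gives no correlations or variances for them, so I put no power figure on those outcomes.

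The illustration in step 4 assumes an effect lasting to day 30. The Discussion cites a meta-analysis that found no difference in resting pain at postoperative days 4, 5 and 7 or at two weeks, so a constant effect is a convenience, not a forecast.

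**Conclusion.** The point holds as one of efficiency. The stated model omits baseline values that the trial collects. For VAS, at the plan's own assumptions, including them would raise omnibus power from 0.80 to between 0.81 (r = 0.1) and 0.91 (r = 0.5). The lower end is negligible and the upper end is worth having; where the trial falls depends on a correlation that the protocol does not give.

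This does not amount to bias, an invalid test or a wrong sample size. Dilution by 7/8, 4/5 or 2/3 is a risk only if the preoperative visit enters as a level of time and the effect is constant. The first condition is unstated and the Abstract speaks against it.

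**What to change.** In Statistical methods {20a}, make three changes:

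1. State that the time factor contains postoperative visits only.
2. Add the preoperative value of the same measure as a covariate for VAS, 1-min walk, each circumference and Knee Society Score, so that the model terms are baseline, group, time and group-time interaction.
3. Report baseline-adjusted mean differences between groups with 95% confidence intervals.

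The adjustment should be tied to the repeated-measures model and not to a single visit, because the primary outcome section names no primary time point. The choice should be fixed before unblinding, so that adjusted and unadjusted results cannot be selected between afterwards. The circumference schedule under Other outcomes should be reworded so that the preoperative measurement is unambiguous.

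The cost is one of 204 between-patient error degrees of freedom (with a common baseline slope), with no new data, no added visits and no change to the sample size.

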## Abstract

**Background:**

Enhanced recovery following total knee arthroplasty (TKA) has been advocated to enhance postoperative recovery. Multimodal cocktail periarticular injection (MCPI) use for pain control in TKA has gained wide acceptance. MCPI-containing corticosteroids are believed to be an effective solution owing to their local anti-inflammatory effects and ability to reduce the local stress response postoperatively. However, there is conflicting evidence regarding its benefits. This trial aims to compare MCPI with a high dose of corticosteroid, normal dose of corticosteroid, and non-corticosteroid during TKA, to assess the effectiveness of MCPI containing corticosteroids in postoperative pain relief, functional improvement, rescue analgesia, and side effects and provide evidence that high-dose corticosteroids result in prolonged pain control and better recovery following TKA.

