### Objectives {7}

We designed a three-arm, randomized controlled trial containing a high or normal dose of MCPI or an MCPI without corticosteroids to assess postoperative pain relief, functional improvement, rescue analgesia, C-reactive protein (CRP), blood sedimentation, blood sugar, and adverse events, thereby evaluating whether high-dose corticosteroid MCPI contributes to prolonged pain control and better recovery.

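### For the primary pain score and the other continuous outcomes, the only pairwise method named is Dunnett's test against a reference arm, which gives no high-dose versus normal-dose contrast although the trial sets out to compare all three formulas

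*Protocol article*

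**What the plan says.** In the protocol article, Statistical methods {20a} gives the pairwise procedures by type of outcome:

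- **Continuous outcomes:** ANOVA across the three groups, after which Dunnett's t "test will be conducted to compare the between-group differences".
- **Repeatedly measured outcomes**, including the primary VAS pain score: a repeated measures ANOVA with group, time and their interaction, and Dunnett's "test will be applied for post hoc comparisons". After a significant interaction, "a one-way repeated measures ANOVA was conducted to identify the difference in effect between the three intervention groups".
- **Categorical outcomes:** "partitions of chi-square methods will be used to compare the between-group differences".

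No reference arm is named for Dunnett's test. Sample size {14} states its two planning differences, 0.8 for H and 0.4 for N, both against control.

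The abstract's Background gives the aim: "This trial aims to compare MCPI with a high dose of corticosteroid, normal dose of corticosteroid, and non-corticosteroid during TKA". It adds that the trial is to "provide evidence that high-dose corticosteroids result in prolonged pain control and better recovery following TKA". Objectives {7} speaks of "evaluating whether high-dose corticosteroid MCPI contributes to prolonged pain control and better recovery".

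**The concern.** Dunnett's procedure is many-to-one. With three arms it makes two of the three possible comparisons. With control as the reference, the missing one is H versus N. If another arm were the reference, a different pair would be missing. The ANOVAs are omnibus tests and cannot attribute a difference to a particular pair.

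A trial with a 7 mg arm, a 21 mg arm and a steroid-free arm invites the question whether the higher dose does more than the lower. Under the stated methods, the only route to an answer on pain, walking distance, swelling or knee score is to note that H reached significance against control and N did not. That is not a test of H against N. Two equally effective doses can fall on opposite sides of the threshold by chance, and the write-up would have no estimate or interval to show it.

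**Working it through.** **Inputs.** Sample size {14}: means relative to control of 0, 0.4 and 0.8 (signs dropped), SD 1.5, α 0.05, 69 evaluable per group. Assumptions made here: two-sided pairwise tests, VAS differences in cm, and a single timepoint analysed by one-way ANOVA with 3 × 68 = 204 residual degrees of freedom.

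**1. The plan's own figure.** The omnibus F test has noncentrality λ = n Σ(μᵢ − μ̄)²/σ² = 69 × (0.16 + 0 + 0.16)/2.25 = 9.81. Power is 80.2% at n = 69 and 79.5% at n = 68, so the stated 69 is reproduced. It is a sample size for the three-group test, not for any one pair.

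**2. Dunnett against control.** The standard error of a difference is 1.5 × √(2/69) = 0.255. The standardised differences are 0.8/0.255 = 3.13 for H–C and 0.4/0.255 = 1.57 for N–C. The two-sided Dunnett critical value for two comparisons is about 2.23 (simulated). Power is then about 82% for H–C and 26% for N–C.

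**3. H significant, N not, when the doses are equal.** Simulated with 69 per arm and SD 1.5. The common effects are illustrative, not from the protocol.

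| Effect of both doses vs control | H significant | Both significant | H only | H only, if the omnibus test must also be significant |
|---|---|---|---|---|
| 0.4 | 26% | 13% | 13% | 10% |
| 0.6 | 55% | 39% | 16% | 14% |
| 0.8 | 82% | 71% | 11% | 10% |

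By symmetry, N only is equally frequent. The article does not say whether Dunnett's test depends on a significant omnibus test, so both versions are shown.

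**4. What an H–N contrast would deliver.** The planning means imply H–N = 0.8 − 0.4 = 0.4. At 69 per arm its power is about 34% at an unadjusted 0.05 and about 22% with Tukey's all-pairs adjustment. The 95% CI half-width is 1.97 × 0.255 ≈ 0.50 cm, wider than the assumed difference. Power of 80% would need about 221 per arm unadjusted, before dropout.

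**5. Omnibus test followed by three pairwise tests at 0.05.** Power is about 79% for H–C, 34% for N–C and 34% for H–N. Ungated Dunnett gives 82% and 26%; Dunnett gated by the omnibus test gives 78% and 26%. Neither gives an H–N result.

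**The case against.** **The objective can be met without H versus N.** Objectives {7} asks whether the high dose contributes to prolonged pain control and does not say more than the normal dose. H versus C answers that, and the planning differences are both against control. This stands: the article nowhere states an H-over-N superiority claim. What remains is the abstract's aim of comparing three formulas. An omnibus test meets that only in the weakest sense, because it cannot say which formulas differ.

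**The analysis plan may add the contrast.** It may, and an article need not list every contrast. Here, however, the article names a specific method, and that method leaves the contrast out. If an all-pairs variant such as Dunnett's T3 or C was meant, the text does not say so.

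**A reader might infer that H versus N is tested nowhere in the trial.** The documents do not support that. Partitions of chi-square can isolate H versus N for categorical outcomes such as the occurrence of adverse events.

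**A reader might also point to the planning means**, under which H is significant and N is not in about 57% of trials (82% − 25% with both significant). That figure is correct arithmetic but a poor measure of harm. Under those means H truly exceeds N by 0.4, so a preference for H would be in the right direction, and the figure mainly reflects low power for N–C. The equal-dose figures measure the risk of a false preference.

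**The calculations simplify the planned analysis.** The primary outcome is measured at seven postoperative times and analysed by repeated measures ANOVA. The percentages are single-timepoint approximations, not operating characteristics of the planned model.

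**Conclusion.** The point holds for the primary VAS outcome and all other continuous outcomes. Read with control as the reference, the stated methods give no H versus N test or interval, while the abstract sets out a three-way comparison and a case for the high dose. The comparisons with control remain valid, and categorical outcomes are not affected.

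The size of the risk is about 10–16%: the chance that two equally effective doses would produce a result in which only H is significant. It rests on illustrative common effects of 0.4–0.8, the plan's SD and evaluable group size, two-sided tests and one timepoint. This should be corrected, but it does not undermine the trial's main comparisons.

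**What to change.** Add to Statistical methods {20a} a prespecified H–N contrast for the primary outcome, at a named timepoint or summary measure, reported with its 95% CI whatever the other results. Rest any statement that the high dose is better than the normal dose on that interval. If H versus N is not of interest, say so and limit the conclusions to each dose versus control. In either case, name the reference arm for Dunnett's test.

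Dunnett's test need not be dropped to do this. If H–N is to be tested formally, an omnibus test at 0.05 followed, if significant, by the three pairwise tests at 0.05 is a closed procedure with exactly three groups. It holds familywise error at 5% for that one analysis, but not across the seven postoperative timepoints.

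The cost is wording, with no extra patients. Two downsides should be stated in the plan. First, H–N has about 34% power and a CI half-width of about 0.50 cm, so it will often be inconclusive, and a non-significant result must not be read as equivalence of the doses. Second, with the omnibus-gated procedure, H–C power is about 79% against 82% for ungated Dunnett.

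### Dunnett's test needs no significant omnibus F before it, and a step-down form would recover power at the same 5% family-wise error

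*Protocol article*

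**What the plan says.** The section on statistical methods for primary and secondary outcomes {20a} states that "Analysis of variance (ANOVA) will be used to compare the differences among the three groups", with Dunnett's t test for the between-group differences. For repeatedly measured outcomes, which include the pain VAS, it names a repeated-measures ANOVA with group, time and their interaction, and adds that Dunnett's "test will be applied for post hoc comparisons". It does not say whether those comparisons are read only after a significant overall test, or whether Dunnett is applied in its single-step or step-down form.

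The sample size section {14} assumes that "the mean difference in the VAS score between the high-dose betamethasone group and control group was 0.8" and that "the mean difference between the normal-dose betamethasone group and control group was 0.4", with an SD of 1.5, α of 0.05, power of 0.80 and 69 evaluable participants per group. The objectives {7} end on the high dose: "evaluating whether high-dose corticosteroid MCPI contributes to prolonged pain control and better recovery".

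**The concern.** Two features of the stated analysis can lose power without buying any error control.

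- **The possible F gate.** Post hoc is often taken to mean that pairwise tests are read only if the omnibus F is significant. Dunnett's critical value already holds the chance of any false claim across the two dose-versus-control comparisons at 5%. A gate can then only discard dose-versus-control results that Dunnett would have declared.
- **The single-step form.** This is the usual meaning of Dunnett's test. It holds both comparisons to the two-comparison critical value even after one of them has been rejected. A step-down version relaxes the threshold for the second comparison at the same family-wise error.

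At stake is the chance of detecting an effect in the dose-versus-control comparisons, and whether the high-dose comparison reaches the plan's own power target.

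**Working it through.** **Inputs.** From the sample size section: effects versus control of 0.4 (normal dose, N) and 0.8 (high dose, H), SD 1.5, α 0.05, n = 69 per group. Sidedness is not stated; two-sided is assumed. The calculation is for one time point, which is how the trial was sized.

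**1. Reproduce the plan's figure.** One-way ANOVA with means 0/0.4/0.8, grand mean 0.4:

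λ = n·Σ(μᵢ − μ̄)²/σ² = 69 × (0.16 + 0 + 0.16)/2.25 = 9.81, on 2 and 204 df.

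Power of the omnibus F is 80.15% at n = 69 and 79.5% at n = 68. So 69 is exactly the omnibus-F sample size.

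**2. High dose versus control (H vs C), Dunnett without a gate.**

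Noncentrality = 0.8/(1.5 × √(2/69)) = 0.8/0.2554 = 3.13. The two-sided Dunnett critical value for two comparisons on 204 df is about 2.23. The noncentral t gives power of 81.7%. For normal dose versus control (N vs C) the noncentrality is half, 1.57, and power is 26%.

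**3. The alternatives, by simulation** (three normal means, pooled variance on 204 df, up to 1,000,000 runs):

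| Procedure | H vs C | N vs C |
|---|---|---|
| Dunnett only after a significant F | 78.1% | 25.5% |
| Single-step Dunnett, no gate | 81.7% | 25.7% |
| Step-down Dunnett, no gate | 82.2% | 33.7% |
| Fixed sequence, H then N, each at 5% | 87.7% | 33.4% |

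The gate removes 81.7 − 78.1 = 3.6 points from H vs C: trials in which Dunnett rejects but F does not.

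Step-down means that the larger statistic is compared with 2.23 and, if it is significant, the other is compared with the ordinary t value of 1.97. The first step is the single-step test, so step-down rejects everything single-step rejects. With no true effects, the simulated chance of any rejection is 5.0%. If both doses truly gave 0.8, step-down would raise power for each from 82% to 86%.

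**4. Sensitivity to n.** If all 78 per group are analysed, H vs C is 83.6% gated and 86.5% ungated; N vs C is 29.0% single-step and 37.6% step-down.

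**5. Sensitivity to repeated measures.** Suppose the comparison is of the mean over the seven postoperative visits, with a constant effect and equal within-patient correlation ρ (assumptions not in the protocol). The SD becomes 1.5 × √((1 + 6ρ)/7):

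| ρ | SD | H vs C gated | H vs C ungated | N vs C single-step | N vs C step-down |
|---|---|---|---|---|---|
| 0.3 | 0.949 | 99.5% | 99.7% | 60% | 69% |
| 0.5 | 1.134 | 96.2% | 97.2% | 44% | 54% |
| 0.8 | 1.365 | 86.0% | 88.7% | 31% | 40% |

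The gate's cost to H vs C shrinks to between 0.2 and 2.7 points. The step-down gain for N vs C stays at about 9 to 10 points.

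**The case against.** Dunnett's test is a valid and standard choice for two doses against a control. Read without a gate it gives 81.7%, above the stated 80%, and the sample size matches the omnibus F exactly, so the sample size and methods sections do not conflict. The text states no gate and never says single-step; both are readings of a short sentence. The single-time-point figures are not the power of a repeated-measures analysis. All of this stands, and it limits the point to lost efficiency and an ambiguity worth closing.

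A reader might go further and infer that the plan ignores its own dose order and should test H vs C first at the full 5%, for about 88% power. The documents do not support calling that a correction. The abstract also asks whether corticosteroid-containing injection works at all, which concerns both doses. The 0/0.4/0.8 pattern is a sizing assumption, and the discussion describes conflicting evidence, including a comparison of high and low doses that found no significant benefit at either. If the order were reversed (normal 0.8, high 0.4), a fixed sequence would cut N vs C power from 82% under ungated Dunnett to 33%. Guarding against that is a legitimate reason to keep Dunnett.

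**Conclusion.** The point holds as a modest and inexpensive improvement, not as an error in the test. An F gate, if intended, costs H vs C about 3.6 points and takes it below the plan's 80% target at 69 per group, without being needed for error control. The single-step form, if intended, costs N vs C about 8 points and H vs C about half a point. These sizes assume two-sided 5% testing, the plan's effects and SD, and a single time point. The loss to H vs C is smaller in a visit-averaged analysis when within-patient correlation is low, and with 78 analysed per group even the gated figure exceeds 80%. N vs C remains underpowered under every procedure on the plan's single-time-point inputs.

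**What to change.** In the statistical methods section {20a}, state that the two dose-versus-control pain comparisons do not depend on a significant omnibus F and are made with step-down Dunnett at two-sided family-wise 5%: the larger absolute statistic against the Dunnett critical value (about 2.23 at 204 df), then, only if that is significant, the other against the ordinary t value (about 1.97). The ANOVA can stay as a descriptive overall test. The 5% applies to one test per dose, so the sentence should name the pain time point or summary measure that it covers.

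The change is to wording only and should be made before unblinding. Its cost is that simple simultaneous confidence intervals no longer match the tests exactly. If the sponsor is willing to rank the doses, a prespecified fixed sequence (H vs C, then N vs C) is an alternative, to be chosen knowing that it allows no confirmatory normal-dose claim when the high-dose comparison fails (about 12% of trials under the plan's assumptions) and performs badly if the order is reversed.
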